#### Background factors at cluster level, for the PHCCs

The background factors for the PHCCs, such as patient demographics, number of patients per PCP, and details of a nurse-led COPD clinic within the PHCC, if applicable, will be registered at baseline and analysed at cluster level.

#### Data storage and security

The research group, i.e. the authors of this paper, will have access to the final trial dataset, and there are no contractual agreements that limit such access for the researchers.

### Randomisation

#### Sequence generation and allocation procedure

The random assignment of the two active intervention groups will be performed by the members of the research group using a computer randomisation programme (http://www.random.org). Our study will not involve any form of restricted randomisation, such as matching or stratification. This is mainly due to the assumption that the participating PHCCs, all from Stockholm County, are fairly homogenous when it comes to size, staff and demographics. Also, earlier research [36] indicate that primary care settings similar to ours tend to possess a fairly low matching correlation (M-rho), hence barely meeting the previously established criterion for significance [37].

To make sure that there is no bias in the group allocation of participants, PHCCs will be selected first before randomisation of clusters takes place. This will be performed in two stages: the first after 3 months of recruitment, and the second after an additional recruitment period, if necessary, for reaching an appropriate sample size. Afterwards, both the research group and the participating PHCCs will be notified about which arm each PHCC will belong to. However, PCPs will sign their informed consent at the first CME session, thus after randomisation is complete. The patients who agree to participate and have signed Informed Consent Forms will fall under the cluster of their PHCCs, but will only be informed about their physicians receiving a CME in COPD and not about which study arm they will be part of.

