### Study design

This study involves a pragmatic and unblinded cluster randomised controlled trial (CRCT) with PHCCs as units of randomisation. In order to isolate the effect of CME, by Case Method, three groups (arms) will be established: one where CME by Case Method will be offered (arm 1, 11 PHCCs), one where traditional lectures (arm 2, 11 PHCCs) will be offered, and one where no CME will be offered at all (arm 3, 11 PHCCs). There will be a total of 33 PHCCs, or 33 clusters, from Stockholm County. From these, 180 PCPs (60 PCPs for each arm) and 460 patients (230 for arms 1 and 2, no patients for arm 3) will be asked to participate. Each PHCC will provide 25–30 patients, which will yield the minimum of 460 patients with COPD in GOLD stages 2 or 3 [2]. The outcome measures will be recorded at baseline and at follow-up which will be after 1 year for PCPs and 1.5 years for patients. The trial design is summarised in Fig. 1 and Fig. 2 as flow charts.

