##### Recruitment of PCPs and data collection

PCPs will be recruited for all three study arms. After agreeing to participate, the manager of the PHCC will receive oral and written information about the study during a face-to-face meeting with the research project manager. The manager of the PHCC then will inform the PCPs that participation in the study will be optional. The PCPs who attend the CME sessions will then, again, be contacted and informed by the CME leader prior to collecting baseline data at the beginning of the first CME session. The reference group will be informed by their manager and by a researcher who will collect baseline data at a specific occasion at each PHCC. By taking the expected response (90%) and dropout rate (20%) into account at the end, the 33 PHCCs will be expected to engage approximately 180 eligible PCPs (60 per arm) whose signed Informed Consent Forms will be required. The PCPs will be informed of their right to withdraw from the study at any time without negative consequences.

The completed questionnaires will be collected by the research group and be put in an envelope and stored in a secure place. The endline data will be collected 1 year after a completed CME during a follow-up visit at each PHCC. The persons who will be absent will be contacted separately to collect their individual endline data.

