##### Recruitment of patients and data collection

Patients will be recruited only for arms 1 and 2, i.e. the intervention and control groups. A total of 990 randomly selected patients with COPD in GOLD stages 2 and 3 [2] (495 in each arm, 40–50 randomly selected eligible patients per PHCC unit) will be invited to participate. With an expected response rate of 60% at baseline and 80% at endline, a total of 230 patients per arm will be included. To ensure the eligibility of the patients, a spirometry slip together with an *International Classification of Diseases, version 10* (ICD-10) diagnosis of COPD (J44.0–J44.9) in the PHCC’s medical records, will be included and reviewed by the research group. Patients with a diagnosis of COPD in the records, but who do not fulfil the criterion of a FEV_1_/FVC ratio <0.7, will be excluded. An independent person, such as a nurse or an administrator, will handle the patient codes for maintaining their anonymity as well as send out the invitation letters. Together with the invitation letter, the patients will receive information about the study, an Informed Consent Form to fill in and the questionnaire (Additional file 2) in a self-addressed envelope to return to the researchers. Two reminder letters will be sent to the patients who have not replied at 2 weeks apart. The patients will be informed that they can withdraw from the study at any time without negative consequences. After receiving the informed consent from the patient, the coding key will be handed over to the researchers. The patient recruitment period will last for 2 months prior to the CME intervention at each PHCC. The endline data will be collected by mail (including two reminders) 1.5 years after the PCPs have completed the CME.

Due to the relatively small-scale collection of data, a Data Monitoring Committee is not deemed necessary.

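### In the two randomised arms, PCPs consent and give baseline data at a first session whose type is already known, so selecting PHCCs before randomisation does not prevent arm-dependent selection of PCPs

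*Protocol article*

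**What the plan says.** The Study design section describes a "pragmatic and unblinded cluster randomised controlled trial (CRCT) with PHCCs as units of randomisation". Under Sequence generation and allocation procedure, three statements follow one another:

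- The safeguard: "To make sure that there is no bias in the group allocation of participants, PHCCs will be selected first before randomisation of clusters takes place".
- The disclosure: "Afterwards, both the research group and the participating PHCCs will be notified about which arm each PHCC will belong to".
- The exception for physicians: "However, PCPs will sign their informed consent at the first CME session, thus after randomisation is complete".

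Recruitment of PCPs and data collection gives the entry route. The manager tells PCPs that taking part is optional. For arms 1 and 2 the text continues: "The PCPs who attend the CME sessions will then, again, be contacted and informed by the CME leader prior to collecting baseline data", and baseline is taken at the start of the first session. Arm 3, which is not randomised, has a separate baseline occasion run by a researcher. PCPs absent at endline are contacted separately; no matching step is stated for baseline.

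Recruitment of the PHCCs says that signed consent forms will come from all PCPs and managers who agree. It gives no date, but the sentence stands just before the one on including and randomising the first 22 PHCCs.

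**The concern.** The safeguard is worded as covering participants, but selecting centres first fixes only which centres are randomised. The arm is then disclosed, and in arms 1 and 2 the individual PCP joins by coming to a session and signing there. The two sessions differ visibly: one is a case discussion that depends on participants' activity, the other a mainly one-way lecture. Attendance could plausibly depend on which is offered, and on the PCP's interest in or knowledge of COPD.

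If so, the PCP samples in arms 1 and 2 could differ before any teaching. The plan names an intention-to-treat analysis and mixed models that tolerate one missing measurement of two. On the described route, however, an eligible PCP who skips the first session has neither consent nor baseline, so no choice of model brings that PCP back. The comparison at stake is the one on physician competence, which the trial's hypothesis uses to explain any benefit to patients.

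**Working it through.** **Order of events, arms 1 and 2, as the protocol gives it**

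1. PHCCs are invited and sign up.
2. PHCCs are randomised.
3. The research group and the PHCCs are told the arm.
4. PCPs attend the first session, or do not.
5. Attenders are informed again by the CME leader, sign consent and complete the baseline questionnaire.

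The safeguard acts between steps 1 and 2. The PCP sample is formed at steps 4 and 5, after disclosure.

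**Reproducing the stated 60 PCPs per arm**

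Inputs: 11 PHCCs per arm and five to ten eligible PCPs per PHCC (Recruitment of the PHCCs); 90% response and 20% dropout (Recruitment of PCPs and data collection). The midpoint of 7.5 is my assumption.

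- Midpoint: 11 × 7.5 × 0.90 × 0.80 = 59.4, which agrees with 60.
- Ends of the range: 39.6 with five per PHCC, 79.2 with ten.

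**How many may be lost at entry**

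- Eligible per arm: 60 / (0.90 × 0.80) = 83.3.
- Consenting at baseline: 83.3 × 0.90 = 75.
- Lost at entry: 83.3 − 75 = 8.3, or about 8 per arm.

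This assumes that the 10% non-response falls at the first session. The 20% dropout comes later and is not part of this step.

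**Largest shift that this loss could cause in one arm**

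Assume a normally distributed score, with the lowest 10% absent in one arm and a random 10% absent in the other. The mean of a standard normal with its lowest fraction p removed is φ(z_p) / (1 − p).

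- p = 0.10: 0.1755 / 0.90 = 0.195 SD.
- p = 0.05: 0.109 SD.
- p = 0.20: 0.350 SD.

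**What an unadjusted comparison would make of it**

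Take 60 PCPs per arm, a two-sided 5% test (sidedness is not stated) and ICC 0.01. That ICC was set for the patient calculation; applying it to PCPs is my assumption.

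- Mean cluster size: 60 / 11 = 5.45.
- Design effect: 1 + 4.45 × 0.01 = 1.045.
- SE: √(2 × 1.045 / 60) = 0.187 SD.
- False-positive rate: 1 − Φ(1.96 − shift/SE) + Φ(−1.96 − shift/SE).

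| Shift (SD) | False-positive rate |
|---|---|
| 0.05 | 5.8% |
| 0.10 | 8.3% |
| 0.195 | 18% |

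With ICC 0.05 the last row becomes 16%. All rows assume that the shift persists undiminished to the analysed score and that nothing is adjusted for.

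**The case against.** **The authors disclose the exception.** The sentence on PCP consent opens with a concession, so it can be said that protection was never claimed at PCP level. That stands in part. Still, the preceding sentence speaks of participants, no remedy follows, and the Discussion's limitations for PCPs do not mention late consent.

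**PCPs hear of the study before the session.** They are contacted by letter at the invitation stage and informed by their manager. This stands: a reader might infer that only attenders are ever approached, and the text says otherwise. Earlier information is not earlier enrolment, however. If the sentence on consent forms in Recruitment of the PHCCs means consent before randomisation, it conflicts with the explicit timing in the randomisation section.

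**Nonresponders are to be examined.** The protocol registers PCP characteristics to describe them and plans an analysis of nonresponse to both questionnaires. It would therefore be wrong to infer that non-attenders leave no trace. Such an analysis describes selection; it does not prevent it.

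**A baseline score exists.** A knowledge difference already present at baseline would largely cancel in a baseline-adjusted comparison. This stands, and is why 0.195 SD and 18% are unadjusted worst cases. Adjustment would not remove differences in motivation that affect how much a PCP gains.

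**The patient comparison.** A reader might infer that patients too are enrolled with the arm known, and that the CCQ result is compromised. The documents do not support this. Invited patients are randomly selected, and eligibility rests on a recorded diagnosis and a fixed FEV1/FVC rule. An independent person sends the letters, researchers receive the coding key only after consent, and patients are not told their arm. The timing sentence, "The patient recruitment period will last for 2 months prior to the CME intervention at each PHCC", dates recruitment against the CME, not against disclosure of the arm.

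**Conclusion.** The point holds for the PCP outcomes in arms 1 and 2. Those samples are formed after the arm is known, and selecting PHCCs first protects cluster allocation only. The order of events is explicit in the protocol and needs no assumption, apart from the unresolved sentence on consent forms.

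The size is less certain. A loss of about 8 of 83 eligible PCPs per arm rests on the plan's 90% and 20% rates and on placing the non-response at the first session. The shift of about 0.2 SD further assumes a normal score, complete selection on that score in one arm, random loss in the other and no baseline adjustment. The documents give no attendance or consent rates by arm, so the actual bias could be close to zero.

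It would be wrong to multiply the two rates and treat 72% retention (0.90 × 0.80) as the measure of this problem, because the later 20% dropout is a separate matter. Nor does the point reach the primary outcome. The trial is powered on patient CCQ, there is no power calculation for PCPs, and which PCPs sit the test does not change the patient analysis set.

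**What to change.** **If PCPs can still be enrolled before disclosure.** In arms 1 and 2, take consent and the baseline questionnaire from all eligible PCPs at the information stage, before the PHCC is told its arm. Follow all of them at 1 year whatever their attendance, and analyse them as allocated with adjustment for baseline score. The cost is one separate questionnaire round in these arms, as arm 3 already has, and later notification of the arm.

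**If enrolment has closed.** The Trial status section places completion of recruitment in 2016 and the article appeared in April 2017, so this is the likelier case. Then:

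- limit the no-bias statement under Sequence generation and allocation procedure to the allocation of clusters;
- adjust the PCP comparison for baseline score;
- report eligible, attending and consenting PCPs by PHCC and arm;
- state among the limitations that the PCP comparison is open to selection after randomisation.

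This costs some analysis and reporting work, plus reconstruction of the number eligible at each PHCC.

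**In either case.** Reconcile the consent sentence in Recruitment of the PHCCs with the randomisation section, so that the protocol states one time at which PCPs consent.

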### Statistical methods

The cluster randomised design provides protection against contamination across trial groups when trial patients are managed within the same PHCC [38]. All analyses will be performed on the individual level adjusted for clustering. Socioeconomic and demographic factors will be taken into consideration, by adjusting for these factors in the models. We have chosen mixed models because this method allows missing data on one of the two measurements. Primary analyses will include intention-to-treat analysis and per-protocol analysis.

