### Participants

#### Eligibility

The study will include 33 PHCCs (clusters) in Stockholm County with more than 10,000 registered patients in each PHCC. Patients with COPD at stages 2 or 3 according to the GOLD criteria [2] who will be willing to participate will be included in the trial. Within each cluster, the participating PCPs will have acquired specialist training in family medicine with a minimum of 5 years of completed or ongoing training, according to the requirements by the National Board of Health and Welfare in Sweden http://www.socialstyrelsen.se/english/Documents/Doctors-specialist-medical-training-National-Board-of-Health-and-Welfare.pdf. To minimise the dropout risk due to short-term employments, temporary PCPs working or training at a PHCC will be excluded, though, by attending CME sessions, they may have an impact on study outcomes.

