#### Recruitment of PHCCs and participants

##### Recruitment of the PHCCs

In Sweden, almost all PCPs are employed by PHCCs, which are medical centres run by county councils directly or by contracted private companies. According to the policies of county councils, all PHCCs must provide the general population with certain primary care services that are carried out by PCPs and district nurses. In practice, all COPD patients in GOLD stages 2 and 3, and many in stage 4, are identified, examined and managed entirely in primary care. Primary care rehabilitation units in Stockholm County are often independently organised and managed separately from PHCCs.

Managers and PCPs of all 80 medium-sized or larger PHCCs (defined as caring for more than 10,000 registered patients, typically yielding five to ten eligible physicians per PHCC), which represent 40% of all 205 PHCCs in Stockholm County, will be contacted by a letter (by post and e-mail) which will serve as an invitation to participate in the study. To meet the required number of patients determined by the power calculation, a minimum of 11 PHCCs per arm will be needed. The number of PHCC depends on access to spirometry results, since a spirometry-verified COPD diagnosis is needed for inclusion. In Stockholm County primary care, there are currently technical and patient confidentiality issues that prevent the collection of data from digitally shared medical records, thus limiting access to spirometry results. Socioeconomic and demographic factors as well as characteristics of the PHCC, such as staffing and access to a nurse-based asthma/COPD clinic within the PHCC, will be taken into consideration during the data analysis and appropriate adjustments will be made for these factors in the models. Signed Informed Consent Forms will be obtained from all PCPs and managers who agree to participate. The first 22 PHCCs signing up will be included in the study and randomised into one of the two interventions arms. The remaining PHCCs with more than 10,000 registered patients will be contacted and the first 11 that accept participation will form a reference group. These PHCCs will not receive a CME, which makes randomisation into a reference arm difficult to motivate ethically.

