#### Primary outcome measures for patients

A patient questionnaire (Additional file 2) consisting of three validated self-report instruments and study-specific questions will be used. The primary outcome measure will be the mean total score in *The Clinical COPD Questionnaire* (CCQ) which is a validated, self-administered questionnaire specifically developed to measure clinical control in patients with COPD [14]. It consists of 10 items, divided into three domains: symptoms, functional state, and mental state (scale per each item: 0 = best, 6 = worst). The higher the score, the greater the negative impact on quality of life and health status. The final measure is the mean value of the 10 questions; Minimal Clinically Important Difference = 0.44 of the final score (mean value) [28]. We will adjust for CCQ at baseline and the CCQs with the minimum of 6 of 10 items replied will be included in the analysis. The CCQ is constructed as an ordinal scale, and the statistics will be analysed accordingly. However, since the CCQ, as most symptom scales, is practically an interval scale, we will present the results using the mean instead of the median, to be able to compare our observations with those of earlier studies [29, 30].

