#### Patient data

Cluster-adjusted regression models will be used for all kinds of outcomes, with both dichotomous and ordinal variables. Cluster-adjusted analysis of variance and linear regression will be used for continuous and normally distributed variables. Mann-Whitney tests will be used for nonparametric variables. The cluster-adjusted chi^2^ test (and cluster-adjusted logistic regression) will be used to compare proportions. Where appropriate, comparisons of arithmetic or geometric means will be performed. A possible substantively important imbalance arising on baseline variables will be controlled at the analysis stage, as adjustment for imbalanced variables. We intend to adjust for multiple comparisons, table-wise, by applying False Discovery Rate, based on the obtained *P* values.

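### Adjustment for disease severity depends on observed baseline imbalance, although spirometry and GOLD stage are conditions of entry; prespecifying one severity covariate is a cheap, minor improvement

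*Protocol article*

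**What the plan says.** All references are to the protocol article.

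- Statistical methods, general rule: "Socioeconomic and demographic factors will be taken into consideration, by adjusting for these factors in the models".
- Recruitment of the PHCCs, adjustment for the type of patient population and centre: "Socioeconomic and demographic factors as well as characteristics of the PHCC". Staffing and access to a nurse-based asthma/COPD clinic are given as examples.
- Primary outcome measures for patients: "We will adjust for CCQ at baseline". No equally explicit sentence exists for CAT, LINQ, exacerbations or hospitalisations.
- Statistical methods, model type: "We have chosen mixed models because this method allows missing data on one of the two measurements".
- Patient data, rule for other baseline variables: "A possible substantively important imbalance arising on baseline variables will be controlled at the analysis stage, as adjustment for imbalanced variables".
- Availability of severity at entry. Eligibility: "Patients with COPD at stages 2 or 3 according to the GOLD criteria". Recruitment of the PHCCs: "since a spirometry-verified COPD diagnosis is needed for inclusion". Recruitment of patients and data collection: "To ensure the eligibility of the patients, a spirometry slip together with an" ICD-10 diagnosis is reviewed by the research group, which also checks the FEV1/FVC ratio.

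FEV1 and GOLD stage are not named as covariates anywhere.

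**The concern.** Read together, these sentences form a covariate rule. Some classes of variable always enter, and the rest enter only if the arms are seen to differ. Severity is in the second group by default, although it defines the study population and is plausibly prognostic for health status, exacerbations and hospitalisation.

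An imbalance trigger is a poor way to choose covariates, for three reasons:

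- In a linear model, a prognostic covariate reduces residual variance whether or not it is balanced. Chance balance is no reason to omit it.
- The decision is taken after seeing the data, in a trial described as unblinded.
- In a logistic model, adding a prognostic covariate changes the odds ratio being estimated. The trigger therefore lets the data decide which odds ratio is reported.

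Randomisation of the 22 centres is neither stratified nor matched, so the design does nothing to hold the stage mix equal between arms.

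At stake are some precision and a fully prespecified model. The validity of the primary comparison is not in question.

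**Working it through.** **The plan's own figures.** Recruitment: 495 × 0.60 × 0.80 = 237.6 per arm, or 990 × 0.60 × 0.80 = 475 in total, which covers the stated 230 per arm (460). With 11 clusters per arm the mean cluster size is 230/11 = 20.9. At the stated ICC of 0.01 the design effect is 1 + (20.9 − 1) × 0.01 = 1.199. The 230 itself cannot be re-derived, because power is not stated and the wording on the standard deviation is ambiguous. It is taken as given here, and the point does not rest on it.

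**Gain on CCQ, given baseline CCQ.** The documents give no correlations, so these are assumptions:

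- r, baseline with follow-up CCQ: 0.5 to 0.8
- f, FEV1 with CCQ, the same size at both times: 0.2 to 0.4 in absolute value
- the design effect unchanged by adjustment
- 80% power before FEV1 is added

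For follow-up CCQ regressed on baseline CCQ and FEV1, R² = (r² + f² − 2rf²)/(1 − f²). The share of residual variance removed beyond baseline CCQ is (R² − r²)/(1 − r²), which simplifies to

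f²(1 − r) / [(1 − f²)(1 + r)].

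| Case | r | f | Variance removed | SE lower by | 230 per arm acts like | 80% power becomes |
|---|---|---|---|---|---|---|
| Smallest | 0.8 | 0.2 | 0.04 × 0.2/(0.96 × 1.8) = 0.5% | 0.2% | 231 | 80.2% |
| Central | 0.7 | 0.3 | 0.09 × 0.3/(0.91 × 1.7) = 1.7% | 0.9% | 234 | 80.7% |
| Largest | 0.5 | 0.4 | 0.16 × 0.5/(0.84 × 1.5) = 6.3% | 3.2% | 246 | 82.5% |

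The SE column is 1 − √(1 − variance removed). The equivalent n is 230/(1 − variance removed).

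**The same correlations with no baseline score in the model.** The share removed is f², that is 4% to 16%. Then 230 per arm acts like 240 to 274, and 80% power becomes 81.6% to 86.4%. This shows how much of the severity signal baseline CCQ already carries. It is not an estimate for exacerbations or hospitalisations, whose correlations with FEV1 are not given.

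**Chance drift in stage mix.** Assume 25% of patients are in stage 3 and round the design effect to 1.2. The standard deviation of the between-arm difference is √(2 × 0.25 × 0.75/230 × 1.2) = 0.044, or 4.4 percentage points. Suppose stages 2 and 3 still differed by 0.5 CCQ points after baseline adjustment, a generous assumption. One such standard deviation would then move the treatment contrast by 0.044 × 0.5 = 0.022, which is 0.022/0.44 = 5% of the minimal important difference the protocol uses.

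**The case against.** The strongest objection is that this is an article, which names classes of covariate and leaves the itemised list to an analysis plan that is not shown. No sentence excludes FEV1 or GOLD stage. That stands as far as the missing list goes, and the absence of a list is not the point. The imbalance trigger, however, is a stated rule, and it is worse than prespecification whatever list exists elsewhere.

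A reader might infer that the plan gives up material, cost-free precision on its patient outcomes. The documents do not support that:

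- Baseline CCQ is fixed in the primary model and is the same scale measured at entry. Entry is limited to GOLD stages 2 and 3, which narrows the range of FEV1. What FEV1 adds is small, and the drift calculation shows that likely imbalance is small too.
- The variance argument belongs to linear models. In logistic regression, which the plan uses for proportions, adding a prognostic covariate does not shrink the standard error of the log odds ratio and tends to increase it. Power may rise, but the estimate becomes conditional on severity.
- LINQ measures information need, so severity has little evident role there.
- Larger gains for exacerbations and hospitalisations are plausible but cannot be quantified from the documents, and the trial is not powered on them.

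**Conclusion.** The point holds as a minor one. The plan makes adjustment for severity depend on observed imbalance, although spirometry and GOLD stage 2 or 3 are conditions of entry for every patient. For the primary CCQ analysis the expected gain from prespecifying severity is about 0.5% to 6% of residual variance, with a standard error about 0.2% to 3% lower. Those ranges rest wholly on the assumed correlations. For outcomes with no stated baseline adjustment the gain is unquantified and possibly larger. Nothing here suggests that the trial's main conclusion would change. The case for acting is that the change is cheap and takes one choice out of the hands of the observed data.

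**What to change.** In Statistical methods and Patient data, replace the imbalance trigger, as far as severity is concerned, with a prespecified rule:

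- Name one severity covariate: FEV1 % predicted, or GOLD stage 2 versus 3 for all patients if FEV1 % predicted is not complete. The two should not be mixed within one covariate.
- Include it, with the outcome's own baseline value, in the models for CCQ, CAT, exacerbations and hospitalisations, regardless of observed balance. LINQ need not be included.
- For logistic models, state in advance that the reported odds ratio is conditional on severity.
- If both CCQ measurements are modelled as outcomes, give the covariate its own effect at follow-up. A constant effect largely cancels from the comparison of change.

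The cost is a few lines of text and one extra parameter per model (one more where a separate follow-up effect is needed). No new measurement is required, since spirometry is already reviewed for eligibility; the value must be entered in the trial dataset.
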